#### Missing data

We will model missing responses/covariates in our longitudinal models. We will consider missing data mechanisms, including missing completely at random, missing at random, or missing not at random, to handle missing data due to a missed assessment time point, study dropout, or unusable MRIs. The full information maximum likelihood estimation (FIML) method will be used in fitting statistical models including LMM and LVM, which allow incomplete data (i.e., cases with missing data will contribute to the analysis).

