### Power calculation

Power analyses using MRI measures from prior RCTs of medication therapy for the treatment of chronic depression [81, 82] indicated that a sample size of N = 30 participants for each of the 3 arms of the study would afford us a power of 80% to detect a moderate-to-large effect size (Cohen d = 0.5) with an α = 0.05 in each imaging modality (anatomical, task-based fMRI, resting state fMRI, and DTI).

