### Data analysis

Analyses will follow an intent-to-treat strategy comparing patients in the groups to which they were originally randomized.

All data will be scored and rescored by separate staff members and checked for accuracy prior to double entry into a REDCap database. Before conducting inferential statistics, we will explore data using descriptive analyses, data visualization, and examining the distributions of all imaging and clinical data. When necessary for continuous variables used as dependent variables, appropriate transformations to obtain approximate normality will be performed.

We will test a priori Primary Hypotheses in the 60 depressed participants by assessing a treatment-by-time interaction in multiple general linear models with repeated measures analyses in an intent-to-treat analysis applied to our various brain measures as dependent variables, including cortical thickness, task-based fMRI activation, resting state connectivity, and FA & ADC measures. Treatment (high vs low frequency) will be the independent variable. When testing hypotheses, we will account appropriately for the correlation of repeated measures across the two time points of measurement (baseline and 1 year) and the spatial correlation within each of our imaging measures. Covariates will include age and sex of the participants. We will examine parameter estimates and 95% confidence intervals, approximate the p-values of component terms, and estimate effect sizes in our final models. Least squares estimates (or maximum likelihood estimates) and their standard errors will be calculated for all models and plotted to assist in interpretation of significant main effects and their interactions. We will ensure that overall, study-wide Type I error-rate is maintained, correcting for multiple comparisons using False Discovery Rate (FDR). FDR-corrected *p*-values < 0.05 will be color-coded and displayed on a template brain.

The 30 healthy controls will be used to estimate the mean and variance of brain measures in the healthy population quantify the effects of high and low frequency psychoanalysis on brain measures and to aid their interpretation as either normalizing a previously abnormal brain measure or introducing a new brain difference that attenuates symptoms.

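### With one follow-up scan, the likelihood fit as described is biased if scan loss follows symptoms differently by arm; the interim symptom scores should be named as auxiliary variables

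*Protocol article*

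**What the plan says.** All points are from the protocol article.

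- **Primary test (Data analysis).** The primary hypotheses are tested "in the 60 depressed participants by assessing a treatment-by-time interaction in multiple general linear models with repeated measures analyses". The model accounts for "the correlation of repeated measures across the two time points of measurement (baseline and 1 year").
- **Covariates (Data analysis).** "Covariates will include age and sex of the participants". No others are named.
- **Missing data.** The mechanisms to be considered are "missing completely at random, missing at random, or missing not at random, to handle missing data due to a missed assessment time point, study dropout", and unusable scans. One estimation method is then fixed: "The full information maximum likelihood estimation (FIML) method will be used in fitting statistical models including LMM and LVM, which allow incomplete data". The section adds that incomplete cases therefore contribute.
- **Timetable (Table 3).** MRI is done at screening or Visit 1 and again at Visit 5 (Day 365). BDI-II and self-rated QIDS are collected at months 3, 6 and 9 as well as at Day 0 and Day 365.
- **Hypotheses (Brain structure, Brain activation, Psychopathology).** Brain change is expected to correlate with, mediate or be associated with clinical improvement.

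Nothing in the article gives the interim symptom scores a role in the imaging models or in the handling of missing scans.

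**The concern.** Likelihood estimation earns its reputation for dropout when there are several follow-up values and the earlier ones carry information about the later ones. Here there is a single follow-up value. A patient who leaves before Day 365 has no earlier post-baseline scan to lend information, so the fit can draw only on arm, baseline scan, age and sex.

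By the plan's own hypotheses, symptom course during the year is informative about the missing scan. If patients who are not improving are lost more in one arm, the scanned patients in that arm are a better-responding subset. Part of that selection then enters the high-versus-low contrast. The arms differ in burden (3-4 sessions a week against one), and under Intervention and comparator patients in the US and Switzerland pay part of the cost, so unequal loss is possible. The article offers no figure for it.

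**Working it through.** **1. The plan's own figure.** Power calculation claims "a power of 80% to detect a moderate-to-large effect size (Cohen d = 0.5") with 30 per arm. From the printed inputs, two-sided: 0.5 × √(30/2) = 1.936, and Φ(1.936 − 1.960) = 49.1%. If the outcome is a change score with SD √(2(1−r)) and r = 0.75, the effect becomes 0.5/0.707 = 0.707 and power is Φ(2.739 − 1.960) = 78.2%. So 80% needs an unstated baseline to 1-year correlation of about 0.76. That makes the figure unverifiable, not shown wrong. Nothing below rests on it; d = 0.5 serves only as the yardstick.

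**2. What the two-time-point fit uses.** In a likelihood fit to baseline and 1 year, the regression of the 1-year scan on baseline and arm is estimated from patients who have both scans. Baseline-only patients refine the baseline mean and variance. Hence it is close to an observed-case comparison conditioned on baseline.

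**3. Size of the bias.** The inputs are assumed, because the article gives none:

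- true d = 0.5 in brain change
- correlation ρ of brain change with symptom improvement s within arm: 0.3 or 0.5
- 30% of scans lost in the high-frequency arm and 15-20% in the low-frequency arm
- log-odds of loss 1.0 higher per SD less improvement, that is logit p(s) = a − s, with a set to give the loss rate

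The mean of s among scanned patients is m = E[s(1−p)] / E[1−p]:

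| Loss | a | m |
|---|---|---|
| 30% | −1.018 | 0.253 |
| 20% | −1.650 | 0.173 |
| 15% | −2.048 | 0.133 |
| any, unrelated to s | – | 0 |

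The expected contrast is 0.5 + ρ(m_high − m_low):

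| Low-arm loss | ρ = 0.3 | ρ = 0.5 |
|---|---|---|
| unrelated to s | 0.5 + 0.3 × 0.253 = 0.576 | 0.5 + 0.5 × 0.253 = 0.626 |
| 15%, same mechanism | 0.5 + 0.3 × 0.120 = 0.536 | 0.5 + 0.5 × 0.120 = 0.560 |
| 20%, same mechanism | 0.5 + 0.3 × 0.080 = 0.524 | 0.5 + 0.5 × 0.080 = 0.540 |
| 30%, same mechanism | 0.500 | 0.500 |

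The bias is therefore +0.02 to +0.13, or 5% to 25% of d = 0.5, and zero when mechanism and rate are equal. A simulation with 2,000,000 per arm agrees (0.524 to 0.627). Regressing on s as well returns 0.499-0.501.

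**4. With a baseline scan in the model.** A simulation that includes the baseline scan, with loss driven by an observed interim score, gave 0.52-0.63 without that score and about 0.50 with it. The extra standard error at 30 per arm was roughly 1-3% or less.

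**5. Different assumptions, true effect zero.** Here the assumptions were 16-26% loss, log-odds 1.5 per SD, baseline to 1-year correlation 0.5-0.75, and interim score correlated 0.2-0.6 with the 1-year scan given baseline.

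| Loss follows symptoms | Absolute bias (SD) | Type I error, 30 per arm |
|---|---|---|
| alike in both arms | about 0.00 | about 5% |
| in one arm only | 0.03-0.15 | 5-9% |
| in opposite directions | 0.05-0.30 | 6-20% |

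With the interim score in the fit, bias was within 0.006 SD throughout.

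**6. What the scores cannot fix.** If missing scans in one arm differ by an unobserved shift δ, the contrast moves by loss × δ: from 0.10 × 0.25 = 0.025 to 0.30 × 0.5 = 0.15 SD, with or without auxiliary variables.

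**The case against.** The strongest objection is that this is a journal article, with no analysis plan or full protocol at hand, and the choice of auxiliary variables is often settled there. A reader might infer that the plan ignores or excludes the interim scores. The text does not support that. The covariate list is introduced as inclusive, the Missing data section says missing responses and covariates will be modelled, and latent variable models can take auxiliary variables. What stands is narrower: the article does fix a method, and for a single-follow-up outcome that method as described gains little from incomplete cases.

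A reader might also infer that the symptom scores show why patients leave. They do not: they may predict who leaves, but they record no reasons. Nor is a change of therapy setting the same as a lost scan, since those patients are analysed as randomized.

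A third tempting reading is that a reported frequency effect would be partly selection. That needs loss to follow symptoms differently by arm, and the article gives no evidence of it. Burden and cost could explain a higher rate of loss, but not a stronger dependence on improvement. At 30 per arm the standard error of d is about √(2/30) = 0.26 before any loss, so even +0.13 is about half a standard error.

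Naming MNAR beside a MAR-based method might be read as a contradiction. The article says only that mechanisms will be considered and does not claim that FIML handles MNAR, so this calls for clarification.

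Finally, the clean recovery of 0.50 is partly built in, because simulated loss depends only on a score that everyone has. That stands: real patients may leave before the score is taken.

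**Conclusion.** The concern holds in a limited form. With one follow-up scan and only age and sex named as covariates, the FIML fit is close to an observed-case comparison given baseline. It is biased when two conditions hold together: scan loss follows symptom course differently by arm, in strength or rate, and symptoms predict the 1-year scan beyond baseline. Under the assumptions in step 3 the bias is about +0.02 to +0.13 SD on d = 0.5. The wider assumptions in step 5 give larger values only when the arms lose opposite kinds of patient. No dropout rate, arm difference in loss or brain-symptom correlation is documented, so these sizes illustrate the risk and do not predict it. The improvement is still worth making, because the scores are already collected and the loss of precision is small.

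**What to change.** In Missing data, for the imaging outcomes:

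1. Name two or three interim measures as auxiliary variables in the FIML models, for example BDI-II at months 3 and 6, or the last available BDI-II score, and QIDS-SR. Model them jointly with the scan and do not add them as covariates of the treatment contrast: they are measured after randomization and lie on the pathway that Aim 2 studies.
2. State that FIML assumes MAR given these variables and those already in the model.
3. State that MNAR is addressed only by a separate sensitivity analysis that shifts the missing 1-year values by a stated delta, by arm.

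The cost is analysis wording and computing time, with no new data. The model becomes slightly more complex with 30 per arm, which is why the list should stay short. It does not help patients lost before month 3, who have no interim score, and it does not remove truly MNAR loss. The change should be fixed before outcome data by arm are seen.

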## Discussion

The findings of MODE will be relevant for both clinical and basic research in identifying the brain-based mechanisms whereby psychotherapy exerts its therapeutic effects. MODE is, to our knowledge, the first study to investigate the neurobiological changes in response the effects of intensive psychoanalytic psychotherapy. MODE will thus contribute to the methodology of using MRI studies in translational psychotherapy. MODE may be the first in a series of studies combining neurobiological, psychological, and psychoanalytical approaches. It will allow us to establish outcome measures on a neural level that are perhaps more sensitive in distinguishing the differential effects of therapeutic dosing than established behavioral and clinical markers of symptom severity and change can provide.

MODE can also offer an answer to the question of why a relatively large group of patients with major depression respond poorly to treatment. Our initial studies suggest that these are patients who often suffered severe trauma before the age of 7 [51, 121]. MODE may help chronic depression patients with early trauma access a tailored treatment that addresses their specific needs. Because of the extremely high prevalence of depression in populations with early trauma, the development of effective and sustainable therapies for these difficult-to-treat patients is among the most urgent medical imperatives.

This research has a notable strength in its randomized controlled design. Yoking MRI to RCTs can identify neurobiological mechanisms predicting and causally mediating treatment response [80]. Most imaging study designs are associational and performed in samples of convenience. They therefore cannot support causal inferences for identifying disease etiology or treatment effects [80]. We hope to use the predictors that we discover to determine whether we can screen depressed patients for those biomarkers and thereby significantly improve treatment response rates in this highly treatment-resistant population. Identifying these markers will provide a framework for developing personalized care in depressed patients. Identifying the brain-based mediators of therapeutic response will support future efforts to enhance manipulation of those mediators to improve treatment response.

## Data Availability

The datasets generated and/or analysed during the current study will be available on reasonable request to the PIs, via the corresponding author ([contact]).

## Abbreviations

BDI-II: Beck Depression Inventory-II
CTQ: Childhood Trauma Questionnaire
HF: High Frequent treatment
IIP: Inventory of Interpersonal Problems
LAC: Langzeitbehandlungen chronisch Depressiver
LF: Low Frequent Treatment
MDE: Major Depressive Episode
MDD: Major Depressive Disorder
MODE: Multi-level Outcome study of psychoanalyses of therapy-refractory, chronically Depressed patients with Early trauma
MRI: Magnetic Resonance Imaging
NT: No Treatment
OPD: Operationalized Psychodynamic Diagnostics
PAT: Psycho-Analytic Treatments
QIDS: Quick Inventory of Depressive Symptoms
RCT: Randomized Controlled Trial
SCL: Symptom Checklist – 90
SCID: Structured Clinical Interview for DSM Disorders
WAI: Working Alliance Inventory
WAIx: Working Ability Index
